**Methods/Design:**

The current study involves conducting a 12-week physical activity intervention based on SDT and MI to promote physical activity in a racially/ethnically-diverse sample. It is hypothesized that this intervention will successfully increase physical activity in participants. Specifically, it is expected that minorities will experience a greater relative increase in physical activity than Whites within the intervention group because minorities are expected to have lower baseline levels of activity.

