### Hypotheses for the primary outcome: physical activity

*Hypothesis 1A*: White participants will report engaging in more physical activity than participants from minority groups at baseline (i.e., a significant main effect of race/ethnicity).
*Hypothesis 1B*: There will be a greater increase in physical activity from baseline among the intervention groups than among the control groups (i.e., a significant main effect of condition).
*Hypothesis 1C*: There will be a greater increase in physical activity from baseline for minority participants in the intervention groups than White participants in the intervention groups (i.e., a significant race/ethnicity by condition interaction).
*Hypothesis 1D*: Participants in the intervention groups will experience a greater increase in need fulfillment during exercise (i.e., autonomy, competence, relatedness and intrinsic motivation) which will mediate the effect on physical activity.$$ Condition\to Need\  Fulfillment\to Physical\  Activity $$

*Hypothesis 1E*: Participants in the intervention condition will report that their instructor utilizes MI skills more frequently which will mediate the effect on physical activity.$$ Condition\to Instructor\hbox{'}s\  Perceived\  use\  of\ MI\  Skills\to Physical\  Activity $$

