### Participants

An a priori ANOVA power analysis was conducted to determine how large a sample would be needed to detect significant main effects and interactions (G*Power version 3.1.3., 2010). This was estimated using a large effect size (f = 0.50), an alpha level of 0.05, and the power was estimated at 0.80. This power analysis determined that 48 participants are needed in the sample in order to detect a statistically significant change in an effect of this size.

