### Planned statistical analyses

The analysis plan involves a 2 (race/ethnicity) × 2 (condition: intervention vs. control) factorial ANCOVA with pretest scores entered as covariates to test Hypotheses 1A-1C involving physical activity (assessed by the International Physical Activity Questionnaire [63]). Analysis of variance will be used to test Hypothesis 2A involving need fulfillment (assessed by the Basic Psychological Needs in Exercise Scale [65] and the Behavioural Regulation in Exercise Questionnaire [66]), physical activity adherence (assessed by how often participants attend the YMCA six months post-intervention), and psychological well-being (assessed by the Psychological General Well-being Index [64]). When examining whether mediators account for the relationship between intervention condition and physical activity, the Preacher and Hayes [69] nonparametric bootstrap approach will be used (i.e., Hypothesis 1D using the Basic Psychological Needs in Exercise Scale [65] and the Behavioural Regulation in Exercise Questionnaire [66] and Hypothesis 1E assessed by the Client Evaluation of Motivational Interviewing Scale [60]).

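### Hypothesis 1A concerns a race/ethnicity gap in physical activity at baseline, but its assigned test, an ANCOVA adjusted for the pretest, does not estimate that gap

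*Protocol article*

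**What the plan says.** In the protocol article, the section on hypotheses for the primary outcome words 1A as follows: "White participants will report engaging in more physical activity than participants from minority groups at baseline (i.e., a significant main effect of race/ethnicity". Its subject is the pretest score. The next two hypotheses concern change. 1B reads "There will be a greater increase in physical activity from baseline among the intervention groups than among the control groups", and 1C compares the increase between minority and White participants in the intervention groups.

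The section on planned statistical analyses gives all three hypotheses one model, a "2 (race/ethnicity) × 2 (condition: intervention vs. control" layout described as a "factorial ANCOVA with pretest scores entered as covariates to test Hypotheses 1A-1C involving physical activity". The activity measure is the IPAQ.

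The article names no other analysis for 1A. The section on participants enrolled compares baseline characteristics by condition only, and physical activity is not among them. The abstract shows why 1A matters: minorities are expected to gain more "because minorities are expected to have lower baseline levels of activity".

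**The concern.** A covariate is a quantity that the model holds fixed. 1A asks whether two groups differ on the pretest, and the named test compares those groups at the same pretest value. The quantity of interest is conditioned away, and what remains is a statement about follow-up.

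At stake is the interpretation of one listed hypothesis. A non-significant race/ethnicity main effect could be read as no baseline disparity, and a significant one as confirming it, when neither follows. Because the baseline gap is the stated reason for expecting 1C, a reader would want to know whether it exists in this sample.

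**Working it through.** **Inputs.** Table 1 gives 31 White participants, and 20 + 4 + 2 = 26 others. The cells are 15 and 16 White (intervention, control), and 27 − 15 = 12 and 30 − 16 = 14 minority. The article gives no baseline gap, IPAQ standard deviation or pre-post correlation. The values used for these below are assumptions.

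**The plan's own figure.** The participants section states: "This was estimated using a large effect size (f = 0.50), an alpha level of 0.05, and the power was estimated at 0.80". With four cells and noncentrality f²N = 0.25 × 48 = 12, an omnibus F test on 3 and 44 degrees of freedom has power 0.803, so the stated 48 is reproduced (0.802 with one covariate). A single 1-df effect would need 34, or 36 in equal cells, and has power 0.92 at 48. The sample size does not depend on the present point.

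**Step 1: what the race/ethnicity term estimates.** Let Δpre and Δpost be the White minus minority differences at baseline and follow-up, averaged over arms, and let b be the within-group slope on the pretest. The analysis section does not name the time point of the outcome, so take each possibility:

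- Outcome is follow-up IPAQ: coefficient = Δpost − b·Δpre.
- Outcome is change: the slope becomes b − 1, so coefficient = (Δpost − Δpre) − (b − 1)·Δpre = Δpost − b·Δpre, the same as above.
- Outcome is the pretest itself: b = 1 and coefficient = Δpre − Δpre = 0 identically. A numerical fit confirmed this, with every coefficient zero except 1 on the pretest.

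1A is the statement Δpre > 0. No reading estimates Δpre.

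**Step 2: four cases.** Simulation with the cell sizes above, normal data, SD 1, correlation 0.6 (so b = 0.6), two-sided 0.05, 4,000 runs each. The direct test is an unadjusted comparison of pretest scores.

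| Assumed truth | Δpost − 0.6·Δpre | Mean ANCOVA estimate | ANCOVA significant | Direct test significant |
|---|---|---|---|---|
| Gap 1 SD, carried forward only through the pretest | 0.6 − 0.6 = 0 | 0.01 | 4.6% | 97% |
| Gap 1 SD, unchanged at follow-up | 1 − 0.6 = 0.40 | 0.40 | 37% | 96% |
| Gap 1 SD, fully closed at follow-up | 0 − 0.6 = −0.60 | −0.60 | 68%, all in the wrong direction | 95% |
| No baseline gap, 1 SD gap at follow-up | 1 − 0 = 1 | 1.00 | 99.5% | 4.9% |

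**Step 3: smaller gaps that persist unchanged.** Here Δpost = Δpre, so the coefficient is (1 − r)·Δpre.

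- Gap 0.5 SD: 0.5 × 0.5 = 0.25 SD at r = 0.5, and 0.3 × 0.5 = 0.15 SD at r = 0.7. Simulated rejection is 17.8% and 12.3%, against 46.3% and 46.7% for the direct test.
- Gap 0.8 SD: simulated rejection is 34.5% and 21.6%, against 83.7% and 82.8%.

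**Step 4: check on the direct test.** For a two-sample t test the noncentrality is d·√(31 × 26 / 57) = 3.76·d. That gives power 0.46 at d = 0.5, 0.84 at d = 0.8 and 0.96 at d = 1.0. For two groups of about equal size f = d/2, so the last value corresponds roughly to the plan's f = 0.50.

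**The case against.** The strongest reply is about weight. 1A is a descriptive contrast between groups that were not randomised, and it is not an intervention effect. The article lists 1A to 1E together without ranking them, and the abstract mentions the baseline gap only as the reason for expecting 1C. The condition effect for 1B and the interaction for 1C are the same whether or not 1A is tested correctly. All of this stands.

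A second reply is that the size depends on chosen inputs. That also stands. A reader might infer from Step 3 that the ANCOVA always shrinks the gap by (1 − r), but this holds only if the gap persists unchanged. Step 2 shows zero and reversed values under other patterns.

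A third concerns the remedy. Since participants were randomised within site, a reader might infer that the 1A model should include site. But the facilities were chosen for their varied racial/ethnic composition and participants picked their own site, so race/ethnicity and site may be associated. Adjustment would then estimate a within-site difference, which 1A does not ask for. The power figures above also belong to the unadjusted comparison only.

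None of these replies rescues the assignment. A fuller plan might add a baseline comparison, but the article does not leave the method open: it names one, and that one does not test 1A.

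**Conclusion.** The assignment of 1A to the pretest-adjusted ANCOVA is wrong as written. This rests on the algebra in Step 1 and needs no assumption about the data. The planned test can miss a real baseline gap, reverse its sign if the gap closes, or be significant when there was none. The rejection rates are illustrative only.

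Two stronger readings are not supported. A reader might infer that the primary analysis of the intervention is invalid. It is not: the mis-assignment leaves 1B, 1C and the sample size untouched, so the point should be fixed but is not a fundamental defect. A reader might also infer that the investigators will report the race/ethnicity main effect as evidence on baseline disparity. The article does not say how they will report it. It only leaves that misreading open.

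**What to change.** In the section on planned statistical analyses, give 1A its own test: an unadjusted White versus minority comparison of the pretest IPAQ score. If site is of interest, add a site-adjusted version as a sensitivity analysis. Restrict the pretest-adjusted ANCOVA to 1B and 1C, and state that its race/ethnicity main effect is not a test of 1A.

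The cost is one sentence and one extra analysis of pretest data that the ANCOVA already requires, with no change to the sample size. One detail to confirm: the note under Table 2 that lists the pre- and post-test survey does not name the IPAQ, although the analysis section implies a pretest IPAQ score.

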### Hypotheses for secondary outcomes: need fulfillment, well-being, adherence

*Hypothesis 2A*. Participants in the intervention groups will experience a greater increase in need fulfillment, psychological well-being, and physical activity adherence than participants in the control groups (i.e., a significant main effect of condition).

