#### Participants recruited

Participants were recruited using online advertisements (YMCA Facebook website) and hard-copy advertisements that were displayed at the YMCA and throughout the city of Syracuse at public libraries, community centers, churches, etc. If the YMCA members were interested in participating, they completed a survey online through Qualtrics or a hard copy version of the survey in order to determine whether they were eligible to participate in the study. The inclusion criteria mandated that participants were currently healthy enough to exercise once a week, not be pregnant or planning to get pregnant within the next 3 months, were willing to attend an exercise class once a week for 12 weeks, were willing to complete questionnaires at baseline and 12 weeks, allowed the intervention staff to monitor their attendance at the YMCA for 6 months post intervention, and allowed the exercise instructor to create an audio recording of all of the intervention sessions.

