Worksheet and Class Discussion: Assess current level of progress with PA change. If unsuccessful, develop new plan.								✓				
Class Discussion: PA with family, friends and pets									✓			
Class Discussion: Instructor decides on topic and leads an SDT and MI-consistent discussion										✓	✓	
CEMI and Survey about participants’ perception of the study												✓

*Pre and post*-*test survey* The consent form, Demographics (age, sex, race, education, and income information), The Support for Exercise Habit Scale, Basic Psychological Needs in Exercise Scale, Behavioural Regulation in Exercise Questionnaire, The Integrated Regulation Items, and The Psychological General Well-Being Index, *PA* Physical Activity, *Short IPAQ and CEMI* Short version of the International Physical Activity Questionnaire and the Client Evaluation of Motivational Interviewing Scale

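### Hypothesis 2A: three pretested questionnaires get ANOVA with no pretest covariate, which is valid but less precise than the ANCOVA used for the IPAQ; adherence has no baseline from which to increase

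*Protocol article*

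**What the plan says.** Under Hypotheses for secondary outcomes, Hypothesis 2A is that intervention participants "will experience a greater increase in need fulfillment, psychological well-being, and physical activity adherence than participants in the control groups". The effect to be tested is given as "a significant main effect of condition".

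Planned statistical analyses assigns two methods in consecutive sentences. The IPAQ gets a 2 × 2 (race/ethnicity by condition) "factorial ANCOVA with pretest scores entered as covariates to test Hypotheses 1A-1C involving physical activity". For the secondary outcomes, "Analysis of variance will be used to test Hypothesis 2A involving need fulfillment", and likewise adherence and well-being. That sentence names no covariate and does not say whether the dependent variable is the week-12 score or the change.

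The pretests exist. The footnote to Table 2 (Intervention sessions) lists the "Basic Psychological Needs in Exercise Scale, Behavioural Regulation in Exercise Questionnaire, The Integrated Regulation Items, and The Psychological General Well-Being Index" in the pre- and post-test survey, which the table places at sessions 1 and 12. The eligibility criteria, which cover both arms, required that participants "were willing to complete questionnaires at baseline and 12 weeks".

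Adherence is defined differently: "physical activity adherence (assessed by how often participants attend the YMCA six months post-intervention". The Physical activity measure also records YMCA attendance during the intervention. No count from before the intervention is described.

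**The concern.** The hypothesis concerns change, the baseline scores are in hand, and the article already uses the standard way of exploiting them for the primary outcome. It gives no reason for a different method on the three secondary questionnaires. With 57 participants, the baseline score is the cheapest available source of precision for estimating the condition effect on need fulfillment, motivation and well-being. Leaving it out as a covariate means wider intervals and less power for moderate effects. It also makes the estimate more sensitive to a chance baseline difference between arms.

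For adherence the difficulty is one of wording. The hypothesis predicts an increase, but the outcome is measured only after the intervention and has no described starting value.

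**Working it through.** **Inputs from the Protocol article.** 27 intervention and 30 control participants (Table 1); alpha 0.05, power 0.80 and planning effect f = 0.50 (Participants), which is d = 2f = 1.0 for two equal groups.

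**Assumptions, not in the document.** Pre-post correlation r from 0.3 to 0.8; equal variance before and after; a common linear slope; independent participants; all 57 contributing both scores.

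**The plan's own figure.** The noncentral F with λ = f²N, numerator df 3 and four cells gives N = 48 (power 0.803), which matches the article. This confirms the method of calculation; the sample size itself is not at issue here.

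**Residual variance for the condition effect**, in units of the post-score variance:
- post-score ANOVA: 1
- change-score ANOVA: 2(1 − r)
- ANCOVA on the pretest: 1 − r²

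The ANCOVA to change-score ratio is (1 − r²)/[2(1 − r)] = (1 + r)/2, which is below 1 whenever r < 1.

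**Power and detectable difference.** λ = d² × (27 × 30/57)/v = 14.21 d²/v, where v is the variance above. Denominator df is 55 for either ANOVA and 54 for ANCOVA, in a two-group model.

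| r | 0.3 | 0.5 | 0.7 | 0.8 |
|---|---|---|---|---|
| Variance, change-score ANOVA | 1.40 | 1.00 | 0.60 | 0.40 |
| Variance, ANCOVA | 0.91 | 0.75 | 0.51 | 0.36 |
| Post-score N matching ANCOVA with 57 (57/v) | 63 | 76 | 112 | 158 |
| Detectable d at 80% power, post-score ANOVA | 0.76 | 0.76 | 0.76 | 0.76 |
| Detectable d, change-score ANOVA | 0.90 | 0.76 | 0.59 | 0.48 |
| Detectable d, ANCOVA | 0.72 | 0.66 | 0.54 | 0.45 |
| Power at d = 0.5, post-score ANOVA | 0.457 | 0.457 | 0.457 | 0.457 |
| Power at d = 0.5, change-score ANOVA | 0.347 | 0.457 | 0.667 | 0.833 |
| Power at d = 0.5, ANCOVA | 0.492 | 0.571 | 0.736 | 0.870 |
| Power at d = 1.0, post-score ANOVA | 0.959 | 0.959 | 0.959 | 0.959 |
| Power at d = 1.0, change-score ANOVA | 0.879 | 0.959 | 0.998 | 1.000 |

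**Chance imbalance.** The baseline arm difference has SE √(1/27 + 1/30) = 0.265 SD, so it exceeds 0.25 SD in either direction with probability of about 0.35. A 0.25 SD imbalance moves a post-score contrast by 0.25r: 0.125 SD at r = 0.5 and 0.175 SD at r = 0.7. It moves a change-score contrast by 0.25(r − 1): −0.125 and −0.075 SD. ANCOVA removes this shift.

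**Repeated-measures reading.** With two time points, the condition-by-time interaction is the change-score ANOVA. The condition main effect, which is the effect 2A names, would average the pre and post scores, so it halves the expected contrast and does not isolate an increase.

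**The case against.** The strongest reply is that the article never says the baseline is discarded. It leaves the dependent variable open. A predicted increase tested as a condition main effect fits a change-score ANOVA, which does use the pretest. The article also calls its power analysis an ANOVA although the primary model is an ANCOVA, so the label may be loose. This stands: a reader might infer that post scores alone are analysed, and the text does not establish that. It does not remove the point, because the change-score form is also less precise than ANCOVA at every r in the range.

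A reader might also infer that a post-score ANOVA tests the wrong thing or is biased. It is not. Under randomisation, the expected arm difference is the same for post scores and for change, and chance imbalance is already reflected in the standard error. Such imbalance enters a post-score estimate attenuated by r, not in full. None is shown on these scales: Participants enrolled reports only that demographics did not differ significantly.

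The gain also depends on an r that the document does not give, and at r = 0.3 it is only 9% of variance. At the planning effect of d = 1.0 either ANOVA exceeds 80% power, so the loss bites only for smaller effects.

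On adherence, it is fair to say that a during-to-after change could be computed from the attendance records. But attendance during the intervention is already under treatment and is not a baseline. A reader might go further and say that visit counts with many zeros rule out ANOVA. No attendance distribution is given, so that does not follow.

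**Conclusion.** The point holds as one of efficiency and wording, for secondary outcomes. For the needs scale, motivation questionnaire and well-being index, the named method is valid but gives up precision that the trial's own data would supply. Relative to post-score ANOVA, ANCOVA cuts variance by 9% to 64% for r from 0.3 to 0.8. Relative to change-score ANOVA, it cuts variance by 35% at r = 0.3, falling to 10% at r = 0.8, from (1 + r)/2. The direction does not depend on which ANOVA is meant; the size depends on the assumed r, on equal variances and on complete data from all 57 participants. The documents do not support calling the planned tests invalid, baseline imbalance an observed fault, or the trial underpowered at its own planning effect.

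The pretest argument does not extend to adherence. There the fault is only that an increase is predicted for an outcome with no described pre-intervention value.

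**What to change.** In Planned statistical analyses, replace ANOVA for the needs scale, motivation questionnaire and well-being index with the race/ethnicity × condition ANCOVA already specified for 1A-1C: week-12 score as the outcome, and that scale's own session 1 score as the covariate. Test 2A through the condition effect.

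In Hypothesis 2A, separate adherence from the other outcomes and state it as a between-arm difference in YMCA attendance over the six months after the intervention.

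The cost is a few words in two sections and no new data. The pretest uses one degree of freedom: with 57 participants, a 2 × 2 ANOVA leaves 57 − 4 = 53 residual degrees of freedom and the ANCOVA leaves 52. If a one-way ANOVA was intended for 2A, the race/ethnicity and interaction terms use two more.

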#### Intervention sessions

The MI techniques that will be used in the intervention sessions are primarily based on information from the books, Motivational Interviewing, Third Edition: Helping People Change and Motivational Interviewing in Groups [48, 49]. The Diabetes Prevention Program, a motivational program to increase physical activity and healthy eating, informs some of the curriculum that will be used during the intervention [50]. Additionally, articles by Williams et al. [51] and Edmunds, Ntoumanis, & Duda [37] inform the SDT techniques that will be used within the intervention. The content of the intervention sessions are described in Table 2. The exercise instructors have some flexibility during their classes in regards to what they decide to discuss within the class. There are two sessions (session 10 and 11), which are not designed to include specific material. Therefore, the instructors can decide to change the treatment protocol by discussing any issues that they believe would help the class during two sessions. They can decide to implement these sessions any time after the first session. The instructors’ standardized treatment manual will facilitate SDT- and MI-adherent conversations, but the program will be tailored to the needs of the group.

**Table 2 Tab2:** Activities during the twelve intervention sessions

	Sessions											
	1	2	3	4	5	6	7	8	9	10	11	12
Aerobic and muscle-strengthening exercises	✓	✓	✓	✓	✓	✓	✓	✓	✓	✓	✓	✓
Pre and post-test survey	✓											✓
Worksheet: Music for class and how to use Facebook page	✓											
Worksheet and Class Discussion: Values, goals, and how PA fits in their lives		✓										
Worksheet: Types of PA they enjoy, Class Discussion: What they know about PA, more information about PA			✓									
Short IPAQ and CEMI				✓				✓				
Class Discussion: Feedback about the PA they do versus the CDC Guidelines				✓								
Worksheet and Class Discussion: If participant wants to change the amount or type of PA they do, confidence strengthening worksheet; if participant doesn’t want to change their PA, barriers to change worksheet.					✓							
Worksheet and Class Discussion: If participant want to change PA, signed contract describing their plan to change; if they don’t want to change PA, barriers to change worksheet.						✓						
Instructor has individual discussions with participants who do not have a plan to change their PA.							✓					

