### Treatment fidelity measures

#### MI techniques

Exercise instructors’ MI proficiency will be assessed at both the instructor-level and at the participant-level. The percentage of MI-adherent responses will be audio recorded using the Motivational Interviewing Treatment Integrity Code (MITI), version 3.1.1 [59]. The experimenter will code every fourth session to detect MI-adherent responses within the language that the exercise instructors use while interacting with participants. Instructors’ MI proficiency will also be assessed by the students in their classes. The Client Evaluation of Motivational Interviewing Scale [60] will be used to assess whether the participants perceive the exercise instructors to be using MI skills every fourth session. This sixteen item scale assesses two subscales: relational and technical factors associated with MI proficiency using a 4 point Likert scale which varies from 1 (never) to 4 (a great deal). An example of the relational factors includes the item, “The exercise instructor changed the topic when I became upset about changing my behavior.” A technical item is, “The exercise instructor helped you talk about changing your behavior.”

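### The mediation plan for Hypotheses 1D and 1E sets no time order; for 1D the schedule makes mediator and post-test activity concurrent, while for 1E ordered data exist but are not specified

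*Protocol article*

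**What the plan says.** Under the hypotheses for the primary outcome, 1D states that need fulfilment during exercise (autonomy, competence, relatedness, intrinsic motivation) will rise more in the intervention groups, "which will mediate the effect on physical activity". 1E makes the same claim for the instructor's perceived use of MI skills. Each is drawn as an arrow diagram from condition to mediator to activity.

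Under Planned statistical analyses, the method is fixed by name: a "nonparametric bootstrap approach will be used". The instruments are then listed: the needs scale and the exercise-regulation questionnaire for 1D, and "Hypothesis 1E assessed by the Client Evaluation of Motivational Interviewing Scale". No session, lag or covariate is given for either mediation model.

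The schedule is in Table 2 and its legend (Intervention sessions):

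- The pre and post-test survey is ticked at sessions 1 and 12 only. Its legend lists "Basic Psychological Needs in Exercise Scale, Behavioural Regulation in Exercise Questionnaire, The Integrated Regulation Items".
- "Short IPAQ and CEMI" is ticked at sessions 4 and 8, and the CEMI again at session 12. This agrees with the section on MI techniques, where the scale is used "to assess whether the participants perceive the exercise instructors to be using MI skills every fourth session".
- YMCA attendance is followed for six months after the intervention (Primary outcome measures).

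**The concern.** A mediation claim needs the mediator to come before the outcome. When both are measured at one visit, the bootstrap tests whether condition shifts the mediator and whether mediator and outcome are associated given condition. The second part is symmetric: it is met as readily when activity drives the mediator as when the mediator drives activity. People who have become more active may feel more competent at exercise, or may rate their instructor more favourably.

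Both mediation hypotheses sit under the primary outcome, and the Discussion frames the trial around a change in motivation with a corresponding change in activity. A positive same-session result would probably be reported as the mechanism, although the data could not show its direction.

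**Working it through.** **Plan's own figure.** The only sample-size figure is 48, from an ANOVA calculation with f = 0.50, alpha 0.05 and power 0.80. It reproduces with 4 groups and 3 numerator degrees of freedom (power 0.803). It concerns main effects and interactions, so the plan has no mediation figure to check.

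**Step 1: which scores exist.**

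| Measure | Session 1 / pretest | 4 | 8 | 12 | Later |
|---|---|---|---|---|---|
| Needs and motivation scales (1D mediators) | yes | no | no | yes | no |
| CEMI (1E mediator) | no | yes | yes | yes | no |
| Short IPAQ | – | yes | yes | – | no |
| IPAQ pretest / post-test | yes | – | – | inferred | no |
| YMCA attendance | – | during the intervention | | | 6 months |

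The session-12 IPAQ is an inference. The Table 2 legend does not list the long IPAQ. However, eligibility required questionnaires at baseline and 12 weeks, the Measures section lists surveys at pre-intervention and sessions 4, 8 and 12, and the ANCOVA adjusts for pretest scores. Table 2 describes intervention sessions; I take the Measures section, which speaks of participants generally, to mean that control participants complete the same surveys.

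So 1D has one post-randomisation mediator score, at the post-test. 1E has two earlier mediator scores, each with a concurrent short IPAQ.

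**Step 2: why a same-session test can mislead.** Inputs: 27 and 30 participants (Table 1). The rest is assumed: activity variance 1, correlation 0.5 between occasions, condition effect on activity d = 0.5 SD at sessions 8 and 12, activity-to-mediator slope s = 0.3 to 0.5, direct condition-to-mediator effect g = 0, 0.5 or 0.8 SD, and no effect of mediator on activity.

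- First path: g + s·d. The standard error is about √(1/27 + 1/30) = 0.265. With g = 0 the path is 0.15 to 0.25, or 0.6 to 0.9 standard errors. With g = 0.5 it is 0.65 to 0.75, or 2.5 to 2.8. With g = 0.8 it is 0.95 to 1.05, or 3.6 to 4.0.
- Second path, same session, adjusted for condition and pretest activity: slope = 0.75s / (1 − 0.25s²), giving 0.23 (s = 0.3) and 0.40 (s = 0.5), although the true effect is zero. The partial correlations are 0.26 and 0.45. With 57 − 4 = 53 degrees of freedom, t is about 2.0 and 3.6.
- Second path, session-8 mediator adjusted also for session-8 activity: zero in this model, because once session-8 activity and condition are held fixed the mediator is only noise.

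The false second path is therefore present throughout. Whether the indirect effect is declared depends mostly on the first path, and so on g.

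**Step 3: simulation.** 1,000 trials per setting, 500 resamples, percentile 95% interval; share of intervals excluding zero:

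| g | s | Same session | Session-8 mediator, pretest only | Session-8 mediator, pretest + session-8 activity |
|---|---|---|---|---|
| 0 | 0.3 | 4% | 1% | 0.1% |
| 0 | 0.5 | 15% | 2% | 0.3% |
| 0.5 | 0.3 | 30% | 9% | 3% |
| 0.5 | 0.5 | 77% | 16% | 5% |
| 0.8 | 0.3 | 47% | 10% | 5% |
| 0.8 | 0.5 | 91% | 21% | 5% |

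**Step 4: sensitivity.** If session-8 activity is recorded with extra error (SD 0.7; 500 trials per setting), the last column becomes 0.4% to 8%. A different activity model, in which each activity score depends on the preceding one, with g = 0 and a condition parameter of 0.5 to 1.0, gave 6% to 41% for the same-session test and 0.5% to 3% for the session-8 version.

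**The case against.** The strongest objection is that the analysis section names no session at all. A reader might infer that the plan puts mediator and outcome at the same session for both hypotheses. The documents do not support that for 1E: the CEMI is collected at sessions 4, 8 and 12, and the text is compatible with using an earlier score. Which score enters the model could properly be settled in a fuller protocol or an SAP that is not shown. That stands, and for 1E the point is only that ordered data are in hand and should be named.

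A reader might also infer that earlier mediator scores are available for both hypotheses. For 1D they are not, beyond the baseline. But this is why 1D cannot be left to a later document: no analysis plan can supply a mid-intervention needs score that was never scheduled.

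Third, the 1D concurrency rests on the outcome being the session-12 IPAQ. The mediation sentence says only physical activity, and attendance is also listed under that outcome. This is fair and is carried as an assumption.

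Fourth, it would be tempting to quote a high false-mediation rate without conditions. That is not supported: without a direct condition effect on the mediator, the rate in the main simulation is at most about 15%.

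Finally, the test of condition on activity (1B) is by ANCOVA and is untouched by any of this.

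**Conclusion.** The point holds in a limited form. The plan states causal chains for 1D and 1E without fixing a time order. For 1D the schedule makes mediator and post-test IPAQ concurrent, on the inference that the latter is at session 12, so the planned bootstrap cannot tell mediation from activity raising need fulfilment. For 1E the order is open and can be secured from data already scheduled.

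The size rests on assumed effects. At an activity effect of 0.5 SD and a reverse slope of 0.3 to 0.5, false mediation under a same-session test is roughly 0% to 15% with no direct condition effect on the mediator. With a direct effect of 0.5 to 0.8 SD it is roughly 30% to 80%, reaching about 90% in the least favourable corner. Hypotheses 2A and 1E predict that condition raises need fulfilment and perceived MI use, so the second range is closer to what the trial expects; the exact size of that effect is not in the documents. The session-8 analysis brings the rate to about 0% to 5%, somewhat more if session-8 activity is poorly measured. It does not remove other unmeasured common causes of mediator and activity.

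**What to change.** - **1E:** name the session-8 CEMI as mediator of the post-test IPAQ, with pretest IPAQ and session-8 short IPAQ as covariates. This needs analysis wording only.
- **1D:** if session 8 has not yet taken place, add the 11-item needs scale and the intrinsic-regulation items to the survey already given there, and analyse them in the same way. This costs participants a few minutes.
- **1D, if no items can be added:** adjust session-12 need fulfilment for its pretest score and report the result as an association only. Use six-month YMCA attendance as a supplementary later outcome. It measures facility use rather than overall activity, and the plan assigns it to 2A, so it should not replace the IPAQ.
- **Both:** state the session of mediator and outcome, and the session at which the post-test IPAQ is given. Label any same-session mediation result as associational.

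The session-8 adjustment has a price. It is conservative, because it removes any effect already reached by session 8, and it may mix the short IPAQ as covariate with the long IPAQ as outcome. Both should be stated alongside the result.
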